## Abstract

**Background:**

Prior studies have shown that meal composition may affect the metabolic responses and arterial stiffness indices, and these responses may be different in lean and obese adults. The primary objective of this study is to determine the feasibility of conducting a trial to compare the effect of three test meals in lean and obese men. Due to the lack of a comprehensive study that concurrently compares metabolic responses and vascular stiffness indices after receiving three different meals in lean and obese men, this pilot study will be conducted with a three-phase parallel design, aiming to investigate the effects of meal composition on the metabolic parameters and arterial stiffness indices of lean and obese adults.

**Methods:**

This pilot, a parallel clinical trial will be performed on 24 male adults aged 18–35 years since January 2021 and will continue until March 2021 who are disease-free and selected based on the inclusion and exclusion criteria at Mashhad University of Medical Sciences, Iran. The subjects will complete three interventions at a 1-week interval, including high carbohydrate (70% carbohydrates, 10% protein, 20% fat), high protein (30% protein, 50% carbohydrates, 20% fat), and high-fat meal (50% fat, 40% carbohydrates, 10% protein). Postprandial effects will be assessed within 360 min after each meal, including the energy expenditure component (resting energy expenditure, thermic effects of feeding, respiratory quotient, and substrate oxidation) and arterial stiffness indices (augmentation index and pulse wave velocity). In addition, blood sampling will be performed to measure glucose, insulin, free fatty acids, and lipid profile.

**Discussion:**

The differences in the postprandial responses can affect the metabolic and vascular parameters due to different meal compositions, thereby providing beneficial data for the establishment of new strategies in terms of nutritional education and metabolic/vascular improvement. Also, the results from this pilot study will inform intervention refinement and efficacy testing of the intervention in a larger randomized controlled trial.

**Trial registration:**

Iranian Registry of Clinical Trials; code: IRCT20190818044552N1; registered on August 26, 2019

## Background

Obesity is a multifactorial, complex, and preventable disorder, which is predicted to affect 20% of the world’s adult population by 2030, while 38% of this population is predicted to become overweight. Epidemiological studies have demonstrated that obesity and overweight are important risk factors for cancer, diabetes, premature death, and cardiovascular diseases [1]. Obesity could be caused by genetic factors, high-energy intake, low-energy expenditure, reduced physical activity, low sympathetic activity, decreased fat oxidation, and differences in hormonal responses [2]. Genetic factors play a pivotal role in the prediction of obesity, and the rising trend of obesity has also highlighted the importance of environmental factors in this regard [2]. The leading causes of obesity include increased energy intake (especially from energy-dense and high-fat foods) and reduced physical activity [3].

Dietary macronutrient composition remarkably influences body weight adjustment. In response to acute changes in the dietary macronutrient composition (e.g., increased fat intake), human subjects have reported the increased oxidation of carbohydrates and total energy expenditure (TEE). Moreover, the short-term changes in the energy intake of human subjects have been shown to stimulate hormonal and metabolic alterations [4]. Postprandial TEE and thermic effect of feeding (TEF) are the main objectives in the management of energy balance, with TEF contributing to postprandial TEE under the possible effect of dietary composition [5–7].

According to human studies, the consumption of animal protein in breakfast leads to less significant changes in the plasma levels of glucose and insulin, while it increased TEF [8–10], and reduced food intake during the day [8, 11]. On the other hand, the vascular function is considered to be a major determinant of coronary artery health, and its disruption could increase the risk of cardiovascular diseases (CVDs) [12]. Previous findings have indicated that the vascular function differs between obese and normal adults in the fasting state [13], while the acute effects of dietary macronutrient composition on the vascular function have not been well documented.

Postprandial hyperglycemia [14, 15], and hypertriglyceridemia [16, 17], have emerged as independent cardiovascular risk factors, promoting interest in the cardiovascular effects of acute dietary exposure. In addition, some findings have demonstrated that postprandial triglyceride (TG) levels may be influenced by the type of lipids, while other studies have shown that saturated fatty acids may induce a slight increase in the levels of postprandial TGs compared to unsaturated fatty acids [18, 19]. A research in this regard indicated that high-fat meals could reduce postprandial cardiovascular reactivity [20]. Another study also demonstrated that diets with high trans fatty acids may increase serum-free fatty acids (FFAs), and high-FFA diets may lead to hyperinsulinemia [21].

Arterial stiffness is an independent risk factor for CVDs, and its intensity may increase in the presence of other CVD risk factors [22, 23]. However, data are scarce regarding postprandial arterial stiffness [24–26], particularly in obese individuals. Aortic pulse wave velocity (PWV) is the ‘gold standard’ for the evaluation of aortic stiffness and subclinical organ damage [27]. Despite the significant association between postprandial lipemia and vascular response, as well as vascular function and arterial stiffness, it remains unknown whether postprandial lipemia directly leads to acute detectable responses in arterial stiffness [28, 29]. According to the above content, prior studies have shown that meal composition may affect the metabolic responses and arterial stiffness indices.

Due to the lack of a comprehensive study that concurrently compares metabolic responses and vascular stiffness indices after receiving three different meals in lean and obese men, the primary objective of this study is to determine the feasibility of conducting a trial to compare the effect of three test meals in lean and obese men and also this pilot study will compare the effects of dietary macronutrient distribution on the metabolic responses (energy expenditure components, postprandial lipemia, and glycemia) and arterial stiffness indices (PWV and pulse wave analysis) of normal and obese adults.

## Methods/design

### Research hypothesis and study time

We will hypothesize that dietary macronutrient composition has different effects on the metabolic responses and arterial stiffness indices of normal and obese adults. The study protocol will be approved by the Research Ethics Committee of Mashhad University of Medical Sciences, and the pilot study will be completed. The study has been initiated since January 2021 and will continue until March 2021. In total, 24 participants (12 obese men and 12 lean men) will complete the interventions and assessments. Data analysis and reporting of the results will be performed until summer of 2021.

### Experimental design

The study protocol is based on the SPIRIT guidelines [30]. Figure 1 depicts the diagram of enrollment, intervention, and assessments. Table 1 shows the schedule of enrollment, intervention, and data collection for each participant. This is a parallel clinical trial, and the subjects will consume three different test meals (high-carbohydrate, high-fat, and high-protein) on different days with a 1-week interval between each intervention.

**Fig. 1 Fig1:**
[figure not shown]
Study diagram of enrollment, interventions, and assessments

**Table 1 Tab1:** SPIRIT 2013 figure showing schedule of enrolment, intervention, and data collection for each participant. ^a^Randomly assigned meal

Timepoint	Study period					
	Enrollment	Allocation	Post-allocation			
	Preintervention	Time 0	Baseline	Intervention visit 1	Intervention visit 2	Intervention visit 3
**Enrolment** Eligibility screen Informed consent Allocation	✓					
	✓					
		✓				
**Interventions** High protein High charbohydrate High fat				✓^a^	✓^a^	✓^a^
				✓^a^	✓^a^	✓^a^
				✓^a^	✓^a^	✓^a^
**Data collection** Food frequency Questionnaire		✓				
International physical activity questionnaires		✓				
Anthropometric variable		✓				
FAT and Lean mass		✓				
Energy expenditure			✓	✓	✓	✓
Resting metabolic rate			✓	✓	✓	✓
Charbohydrate oxidation			✓	✓	✓	✓
Fat oxidation			✓	✓	✓	✓
Protein oxidation			✓	✓	✓	✓
Blood pressure			✓	✓	✓	✓
Heart rate			✓	✓	✓	✓
Augmentation index			✓	✓	✓	✓
Pulse wave velocity			✓	✓	✓	✓
Serum glucose and insulin levels			✓	✓	✓	✓
Lipid profile			✓	✓	✓	✓

### Participants and data collection

Data collection will be performed by two nutritionists and one nurse, who have been trained on the proper use of various devices and are able to complete the questionnaires accurately. Since this is a pilot study, we cannot assess the attrition rate, and it is also not necessary to define and calculate the sample size. Our study follows sample size for pilot trial and aims to have at least 12 subjects per group who provide full data( in total 24 subjects) [31]. This sample size will to provide a pooled standard deviation that provides enough precision for the development of a future study.

### Study setting and sample population

This pilot, a parallel clinical trial will be performed at Imam Reza Hospital of Mashhad, located in the northeast of Iran. The participants will be recruited by local advertising with posters distributed at Mashhad University of Medical Sciences.

### Inclusion criteria

The inclusion criteria of the study are as follows: (1) age of 18–40 years; (2) adults with normal weight (body mass index [BMI]: 18.5–23.5 kg/m^2^, body fat percentage: 12–22%, waist circumference < 90 cm), and obese adults (BMI > 27.5 kg/m^2^, body fat percentage > 27%, waist circumference > 95 cm); (3) apparently healthy men; (4) written informed consent to participate; and (5) willingness to undertake the required fasting periods.

### Exclusion criteria

The exclusion criteria of the study are as follows: (1) professional athletes; (2) greater changes in the bodyweight than 10% within the past 6 months; (3) current smoking habits; (4) use of medications or supplements affecting the metabolism (e.g., thyroid drugs, caffeine); (5) history of CVDs, hypertension, diabetes mellitus, hyperlipidemia, and neurological and/or neuropsychological disorders; (6) consumption of toxic substances; (7) use of supplements for weight loss or weight gain; and (8) inability to partake in the intervention due to intolerance/dietary preferences.

### Test meals

Three interventions will be implemented in the current research, involving the consumption of high-fat, high-carbohydrate, and high-protein meals as the test meals in a randomized order. On the day of the intervention, the TEE of the subjects will be determined via indirect calorimetry. The test meals will contain 25% TEE for men, and the high-protein meal will consist of bread, cheese, boiled eggs, and skimmed milk (30% protein, 50% carbohydrates, and 20% fat). The high-carbohydrate meal will consist of skimmed milk, white bread, butter, jam, and honey (70% carbohydrates, 20% fat, and 10% protein), and the high-fat meal will contain bread, butter, cream cheese, high-fat milk, and jam (50% fat, 10% protein, and 40% carbohydrates). The subjects will be asked to ingest the test meals within a maximum of 15 min on each test day.

#### Outcomes

The primary outcome will to evaluate the feasibility of conducting a trial to compare the effect of three test meals in lean and obese men. The feasibility will be assessed by measuring subject compliance with the intake of three test meals, recruitment, and retention rate in 3 days of study. Also, adherence to sample collection protocol will be assessed. Secondary outcomes will to compare the effect of three test meals on metabolic responses and vascular parameters in lean and obese men for sample size calculation.

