## Statistical analysis

Briefly, descriptive statistics will be used to summarize enrollment adherence, recruitment rates, and dropout. Feasibility outcomes will be presented as percentage and 95% confidence intervals. A retention rate of > 80% will be considered as feasible to conduct a future RCT. Analysis of outcomes will be conducted using both intention to treat. Also, in the analysis of clinical outcomes, descriptive statistics will be used to compare and determine the primary characteristics of the study groups, and the normal distribution of the variables will be evaluated using the Kolmogorov-Smirnov test. In total, 24 subjects have been assigned to the obese and normal groups. The baseline comparisons between the groups will be performed using the independent samples *t* test or Mann-Whitney *U* as appropriate. In addition, repeated-measures analysis of variance (ANOVA) will be used to assess the timing effect of the research parameters in various phases of the study. Data will be used for sample size estimation and to determine the most appropriate outcome measure for the main study.

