## Discussion

The current research aims to investigate the effects of the single ingestion of various test meals on the metabolic responses and vascular reactivity of healthy and obese adults. To the best of our knowledge, no previous research has concurrently assessed the postprandial effects of three meals with various compositions (high-protein, high-fat, and high-carbohydrate) on metabolic and vascular parameters. Based on the study design, the subjects will receive three types of meal on different test days to determine the differences in the metabolic parameters and arterial stiffness indices between the normal and obese subjects.

Considering the design of the present study, the balance in the confounding variables will be ensured in the study groups, and the bias induced by the characteristics of the subjects will be removed. However, the main challenge in this experiment will be the attrition rate and subject compliance as they must attend the study setting on three days, and the study process will continue for almost 7 h for each subject on each test day. Consequently, some of the subjects may fail to complete the three test days due to lengthiness, tardiness, and other reasons. Notably, the researchers will thoroughly describe the principles and requirements to the subjects prior to the experiment in order to ensure their compliance.

Conflicting results have been proposed regarding the effects of meal composition on metabolic and vascular responses. Based on the hypothesis of the current research, our findings will describe the effects of meal composition on metabolic and vascular responses. Given the increasing prevalence of CVDs and their close correlation with dietary habits, lipemia, and glycemia after meals, investigating the effects of meal composition on vascular functions and metabolic responses is of great interest. Furthermore, the subject matter may be incorporated into the design of novel lifestyle and dietary interventions. We recognize that in this pilot study, we are not powered to investigate effects between the different groups. Collecting data on the secondary outcomes such as metabolic and vascular responses will help to inform sample size calculations in future studies.

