## Conclusion

If a significant result is achieved regarding the measured parameters in the pilot study, we will design a study with a larger sample size consisting of both genders. The results of these studies may provide the proper tools to adapt various meal types to different body compositions in order to improve metabolic responses and vascular reactivity.

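### The article names two different pilot inputs for the main study's sample size, the compared meal effects and a pooled SD, and its Conclusion ties the larger study to a significant pilot result

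*Protocol article*

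**What the plan says.** All references are to the protocol article.

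- **Outcomes:** the secondary outcomes are to "compare the effect of three test meals on metabolic responses and vascular parameters in lean and obese men for sample size calculation". The input named is the compared effect.
- **Participants and data collection:** the trial "aims to have at least 12 subjects per group who provide full data", 24 men in total. It says "it is also not necessary to define and calculate the sample size", and that the chosen number is meant "to provide a pooled standard deviation that provides enough precision for the development of a future study". The input named is the SD.
- **Statistical analysis:** "Data will be used for sample size estimation and to determine the most appropriate outcome measure for the main study". It does not say whether effect or SD is meant.
- **Discussion:** the authors recognise that "we are not powered to investigate effects between the different groups", then say that the secondary outcome data "will help to inform sample size calculations in future studies". Again the quantity is not named.
- **Conclusion:** the larger study is to be designed "If a significant result is achieved regarding the measured parameters in the pilot study".
- **Feasibility outcomes and Statistical analysis:** success is judged on recruitment (60% of target), completion (80% or more), and acceptability and adherence. Retention above 80% is taken to show that a future RCT is feasible. Neither section mentions a significant result.

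**The concern.** Two instructions do not fit together.

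First, a pilot SD is an accepted input to a sample size. A pilot effect is not a safe one, because the required number varies with the inverse square of the effect and the effect is poorly estimated here. The article points to both.

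Secondly, going on only after a significant result filters the estimates. In a small study only large observed effects reach significance, so for a modest true effect those that pass are too large. A main study sized on such an effect would miss its stated power. The condition also conflicts with the feasibility criteria given elsewhere in the article.

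**Working it through.** **Inputs from the article.** There are 12 lean and 12 obese men, and each takes all three meals. Meal contrasts are therefore within-man (24 pairs) and lean-obese contrasts are between-man (12 v 12). The pilot size comes from a pilot guideline, without alpha, power, effect or SD, so there is no stated calculation to reproduce.

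**Assumptions.** Two-sided 5% test, normal data, and true effects over a range. Paired effects are in units of the SD of the within-man difference.

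**1. Smallest effect that can be significant.**
- Paired, n = 24: t(0.975, 23 df)/√24 = 2.069/4.899 = 0.42 SD.
- Lean-obese, 12 v 12: t(0.975, 22 df) × √(2/12) = 2.074 × 0.408 = 0.85 SD.

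Any estimate that passes the filter exceeds these values, whatever the truth. With 12 per group, the difference detectable with 80% power is (1.96 + 0.842) × 0.408 = 1.14 SD.

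**2. Paired meal contrast, sized on the median significant effect, 90% target power.** There were 200,000 simulated pilots per row. Sizes and true power come from the paired t test. As a rough check, n ≈ (1.960 + 1.282)²/d² = 10.51/d². At d = 0.3 this gives 117, and the t-based figure is 119.

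| True effect (SD) | Pilots significant | Median significant effect | Men planned | Men needed | True power |
|---|---|---|---|---|---|
| 0.2 | 16% | 0.52 | 42 | 265 | 24% |
| 0.3 | 29% | 0.54 | 39 | 119 | 45% |
| 0.5 | 65% | 0.61 | 31 | 44 | 77% |
| 0.8 | 96% | 0.82 | 18 | 19 | 89% |
| 1.0 | over 99% | 1.01 | 13 | 13 | 91% |

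**3. The same contrast without the filter.** At a true 0.3 SD the observed effect has a 95% range of −0.10 to 0.76 and a median of 0.304. The estimate is noisy but not inflated.

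**4. Lean-obese contrast, 12 v 12, true effect 0.6 SD.** About 29% of pilots are significant, and the median significant effect is 1.08 SD. Per group, n ≈ 2 × 10.51/d², which gives 18 at 1.08 and 58 at 0.6. The ratio is (1.08/0.6)² = 3.2.

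**5. Effect route against SD route.** Lean-obese contrast, true effect 0.5 SD, 80% target power, 63 per group needed:

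| Input taken from the pilot | Planned n per group | Mean true power |
|---|---|---|
| SD only, target difference fixed | 80% range 41 to 88 | about 78% |
| Observed effect, always | 80% range 14 to about 1,290 | about 70% |
| Observed effect, only if significant | median 15 | about 27% |

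The SD itself is not precise. With 22 df its 95% interval runs from 0.77 to 1.42 times the estimate, so the required n runs from 0.60 to 2.0 times. That is still far tighter than the effect route.

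**The case against.** A reader might infer that the plan is settled: the pilot's observed difference becomes the target difference, so the main study will be too small. The documents do not support that. No section says that the observed difference will be the target, and the one section that states what the pilot is sized to supply names the pooled SD. Nor does the lack of a target difference show that the pilot's own must be used. A pilot need not fix the target of a later trial, and a condensed article may leave it out.

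Three further limits stand.

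- The admission about power concerns effects between the groups, which in this article are the obese and normal men. It does not clearly cover within-man meal contrasts, which are more precise.
- Low power alone does not make an estimate too large on average; selection does. The filter rests on one sentence in the Conclusion, against feasibility criteria in the body of the article. Choosing the main outcome from the same data could be a second selection step, but its effect was not calculated.
- For large within-man effects the loss nearly vanishes, and the article gives no effect size that would show where the truth lies.

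The contradiction remains. Outcomes and Participants and data collection name different inputs, and the Conclusion states a condition that the feasibility criteria do not contain. The lean-obese difference in response, where the admitted lack of power applies directly, is also part of the research hypothesis.

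**Conclusion.** The point holds as an inconsistency with a real statistical consequence, not as proof that the main study will be undersized. Taking the Outcomes wording literally gives a very imprecise planned size. Adding the Conclusion's condition also gives an inflated effect when the true effect is modest. The shortfall runs from roughly threefold (0.3 SD paired, or 0.6 SD lean-obese) to almost none (0.8 SD paired). These sizes depend on the assumed effects, a two-sided 5% test, 90% target power, and a planner who uses the observed effect as the target. The correction is worth making because it is cheap and the article's own pooled-SD rationale already supports it.

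**What to change.** - **Outcomes and Statistical analysis:** state, in line with Participants and data collection, that only variability (SD and within-subject correlation) and feasibility rates feed the main study's sample size. An upper confidence limit for the SD would be a prudent choice.
- **Same sections:** state that the main study's target difference will be a smallest difference of interest, set independently of the pilot's observed effects. Report the pilot's meal and group differences with 95% confidence intervals as description only.
- **Conclusion:** replace the condition of a significant result with the criteria in Feasibility outcomes and Statistical analysis.

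The cost is a few sentences now, and agreement on target differences before the main study is sized. The downside is that the planned main study may be larger.
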